#### Sample size determination

*ADA arm*: after 1 year (50 weeks) of treatment, 20.3% of NIU patients achieved an outcome similar to our *primary efficacy outcome*.^28^

*MTX arm*: after 6 months of treatment, 65% of NIU patients achieve also similar outcome;^64^ we estimate that of those patients, 18%^65^ and 16%^66^ will be unable to maintain our outcome due to AEs and inefficacy, respectively; therefore, at 1 year, 43% will achieve our *primary efficacy outcome*. This figure will be assumed as the percentage of subjects treated with monotherapy achieving the primary efficacy outcome.

*MTX+ADA arm*: we will assume that combination therapy will increase the percentage of subjects achieving our *primary efficacy outcome* by 23% compared with the monotherapy arms.

To detect statistically significant differences between groups with a power of 80% and a significance level of 0.05, it will be necessary to recruit 54 patients per study arm (162 in total). Since the follow-up period is 52 weeks, losses of 15% will be assumed, increasing the sample size to 64 patients per study arm (192 patients in total). In order to test the difference between the treatments, superiority or relevant clinical improvement has been considered from a delta of 5% of the effect.

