#### Planned methods of statistical analysis for efficacy-related objectives

The primary analysis will be a Mantel–Haenszel test (MHT), stratified by NIU location, comparing the combination therapy arm and the single ISDs arms (both arms combined), and performed in the ITT set. Achievement of the Good Clinical response will be considered the binary response variable: those subjects achieving a Good Clinical versus those not achieving the outcome (regardless the cause). The exposure variables will be the treatment arm: those subjects receiving combination therapy versus those receiving either monotherapy. Uveitis location will be the strata: intermediate uveitis versus posterior OR panuveitis. If the results of the primary analysis are significant, then pairwise comparisons using MHT stratified by NIU location will be carried out. P values of the pairwise comparisons will be adjusted using the Bonferroni method. No interim efficacy-related analysis will be carried out.

Secondary efficacy-related analyses are designed to test the hypothesis that treatment assignment affects a given outcome, after controlling for selected covariates. Details can be found at table 4.

**Table 4 T4:** Planned methods of statistical analysis for efficacy-related secondary outcomes

Outcome variable	Statistical analysis
Complete abrogation of the ocular inflammatory signs, which is achieved within the first 16 weeks of the study, no treatment failure due to safety or intolerability; compliance with the initial (up to week 16) oral GCs tapering protocol and completion of all study visits from baseline to 16 weeks	MHT, stratified by NIU location. If p-value<0.05, pairwise comparisons using MHT stratified by NIU location will be carried out with Bonferroni adjustment of the pairwise p-values
EQ5D	GEE models nested by patient^70 71^ and adjusted by study visit (continuous) and treatment arm (discrete) will be carried out, using a Gaussian family and Identity as link function. Different covariable structures will be tested (independent and exchangeable) and compared using the Bayesian Information Criteria. Time x study arm interactions will assess different effects of time in the evolution of the outcome by arm. P-value<0.05 will be considered as a significant interaction
Visual Functioning Questionnaire-25 Hospital Anxiety and Depression Scale	Changes between Baseline and w16, and the FET visit will be compared between treatment groups using ANOVA

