Active chorioretinal lesions; active retinal vascular lesions; macular oedema; ACC; vitreous haze and loss of CVA secondary to inflammation at baseline, week 16, week 52 and relapse visit	MHT, stratified by NIU location. If p-value<0.05, pairwise comparisons using MHT stratified by NIU location will be carried out with Bonferroni adjustment of the pairwise p-values
The time to inflammatory relapse between groups, defined as the time from visit 16 weeks until end of the study, loss of follow-up or appearance of at least one ocular inflammatory manifestation, in those individuals achieving a Good Clinical Response by visit 16 week	Time to relapse between arms will be analysed using log-rank test at a two-sided significance level of 5%. Dropouts due to reasons other than inability to maintain a Good Clinical Response will be considered as censored observations at the time of dropping out. Only subjects able to achieve a Good Clinical Response by visit week 16 will be analysed. We will consider both the time until the onset of the first inflammatory manifestation, each inflammatory manifestation, the first inflammatory manifestation that does not resolve in the following 4 weeks and each inflammatory manifestation that does not resolve in the following 4 weeks.
Best-corrected visual acuity during follow-up	GEE models
Assessment of anti-ADA antibodies (AAA) at weeks 15, 27, 51 and relapse	MHT, stratified by NIU location. If p-value<0.05, pairwise comparisons using MHT stratified by NIU location will be carried out with Bonferroni adjustment of the pairwise p-values
Direct and indirect cost, and incremental cost effectiveness ratios	Cost utility and cost-effectiveness analysis from the perspectives of the National Health System and the Society will be performed. EQ5D scores will derive utility values representing health related quality of life. QALYs will be calculated by the area under the curve assuming a linear evolution of EQ5D values between visits. The average number of QALYs per patient will be calculated for each study arms. Effectiveness will be defined using our primary efficacy outcome. An average cost per patient will be calculated for each study arm, including direct (drug cost, outpatient and inpatient care and other medical cost) and indirect cost (home care, productivity loss): Incremental cost-effectiveness ratios will be calculated, using the MTX monotherapy arm as comparison

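### For the primary outcome, the Bonferroni step on the pairwise tests is not needed for 5% family-wise control once the primary test must be significant first, and it costs power on the only tests that compare the combination with each drug

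*Protocol article*

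**What the plan says.** The section on planned methods for the efficacy objectives sets up two steps for the primary outcome. The first is a Mantel–Haenszel test, stratified by uveitis location, of the combination arm against both monotherapy arms pooled, in all randomised subjects. The second depends on the first: "If the results of the primary analysis are significant, then pairwise comparisons using MHT stratified by NIU location will be carried out". It then adds: "P values of the pairwise comparisons will be adjusted using the Bonferroni method". Neither the number of pairwise comparisons nor the divisor is given.

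Three rows of Table 4 (inactivity by week 16, the individual inflammatory signs, anti-adalimumab antibodies) use the same pattern: a Mantel–Haenszel test, and if it is significant, pairwise tests "carried out with Bonferroni adjustment of the pairwise p-values".

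The sample size section plans "with a power of 80% and a significance level of 0.05". It derives the methotrexate rate ("therefore, at 1 year, 43% will achieve our" primary outcome) and applies it to both single-drug arms: "This figure will be assumed as the percentage of subjects treated with monotherapy achieving the primary efficacy outcome". The combination is assumed to add 23%. The result is 54 per arm, raised to 64 for 15% losses.

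**The concern.** The two layers guard against the same error. A pairwise claim must pass the primary test at 5% and then also a Bonferroni-adjusted test. In a three-arm trial the first layer is enough for 5% family-wise control, so the second lowers the chance of a true finding without being needed for that control.

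This matters because the main hypothesis, under Objectives and outcome variables, is that the combination does better than each drug given alone. The primary test pools the two drugs and cannot show that by itself. Only the pairwise tests can, and the trial is not sized for them.

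**Working it through.** **Inputs.** Combination rate 0.43 + 0.23 = 0.66, reading the 23% as percentage points; monotherapy rate 0.43 in each arm; 1:1:1 allocation; 54 per arm before and 64 after the allowance for losses. The article does not state the sidedness of the primary test. Two-sided 0.05 is assumed: it fits the sample size, and the time-to-relapse row of Table 4 uses a "log-rank test at a two-sided significance level of 5" per cent.

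**Reproducing the plan's figure.** For the combination against the pooled monotherapies (ratio r = 2):

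n = [z₀.₉₇₅ √(p̄(1−p̄)(1+1/r)) + z₀.₈₀ √(p₁(1−p₁) + p₂(1−p₂)/r)]² / (p₁−p₂)²

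with p̄ = (0.66 + 2×0.43)/3 = 0.507. The two terms are 1.200 and 0.496, so n = (1.696/0.23)² = 54.4, or 55 rounded up, against 54 stated. Power at 54 versus 108 is 79.7%. The allowance gives 54/0.85 = 63.5, so 64. A 1:1 two-sided comparison would need 73 per arm. The stated size therefore fits the pooled contrast and not the pairwise ones.

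**Why the primary test is enough.** There are three pairwise nulls of no difference.

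- If two or more are true, all three arms are equal. Any pairwise claim then requires the primary test to reject as well, and that test is a valid 5% test of equality of all arms. The chance of any false claim is at most 5%.
- If exactly one is true, only one false claim is possible, and its own 5% test bounds it.
- If none is true, no false claim is possible.

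This is closed testing. It needs a valid 5% test of the full null, and the pooled contrast is one. The argument is specific to three arms.

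**Family-wise error by simulation.** Stratified Mantel–Haenszel tests, 64 per arm, all three pairs tested, each pair only after a significant primary test. The case of the combination equal to one drug has the other drug at 20.3%. The ranges cover separate runs with and without strata.

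| True state | Unadjusted | Bonferroni over 3 |
|---|---|---|
| All arms equal | 4.3–4.5% | 2.2–2.3% |
| Combination = one drug | 2.4–2.6% | 0.8% |
| Monotherapies equal, combination at 66% | 4.2–4.4% | 1.3–1.4% |

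The highest value in any scenario or sample size tried was 5.3%, which is what a single nominal 5% test shows through simulation noise and discreteness. With all arms equal, three unadjusted tests that do not depend on the primary test would give about 12%.

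**Power.** For one pairwise test at 64 per arm: p̄ = 0.545; null standard error √(0.545×0.455×2/64) = 0.0880; alternative standard error √((0.66×0.34 + 0.43×0.57)/64) = 0.0857. Power = Φ((0.23 − z×0.0880)/0.0857):

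- z = 1.960 (0.05): 75%
- z = 2.241 (0.025): 65%
- z = 2.394 (0.0167): 59%

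Requiring the primary test as well lowers the first to 72–73% and leaves the others almost unchanged. Simulated power with the primary test required (stratified and unstratified runs agree within about one point):

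| | Unadjusted | Bonferroni over 2 | Bonferroni over 3 |
|---|---|---|---|
| Each comparison, 64 per arm | 72% | 65% | 59% |
| Both, 64 per arm | 61% | 50% | 43% |
| At least one, 64 per arm | 84% | 80% | 75% |
| Both, 54 per arm | 51% | 41% | 33% |

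The third row is twice the first minus the second, within rounding (for divisor three, 2×59 − 43 = 75).

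**Sensitivity.** The article also reports that with adalimumab "20.3% of NIU patients achieved an outcome similar to our" primary outcome, but does not use that rate for planning. With adalimumab at 20.3% and 64 per arm, power to win both is 74–75% unadjusted, about 66% over two and 59% over three.

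**The case against.** Bonferroni after a significant primary test is a valid procedure. It leads to no wrong inference and leaves the primary test untouched. It controls the error without relying on the first step, and it has matching simultaneous confidence intervals, which unadjusted tests after a significant primary test do not. All of this stands, and it is why the point is about efficiency.

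Four stronger readings are tempting, and the document does not support them.

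- **That the plan loses 18 points of power, from 61% to 43%.** That needs a divisor of three, which the article never states, and a requirement to beat both drugs, which it does not set as a formal success rule. It also needs all 64 per arm analysed at the planning rates. If both comparisons must succeed, no multiplicity adjustment is needed even without closed testing.
- **That the penalty buys nothing.** It lowers the actual family-wise error, from 4.3% to 2.2% when all arms are equal. It is unnecessary only for staying at the nominal 5%.
- **That the control holds for any pairwise hypothesis.** The sample size section ends with a sentence about superiority from a 5% delta. If the pairwise tests used a non-zero margin behind a zero-margin primary test, two true pairwise nulls would no longer mean equal arms, and the argument would fail.
- **That Table 4 can carry the same 5% statement.** The row on inflammatory signs covers six signs at several visits, with no adjustment stated across them. At one visit, with the six signs taken as independent (an assumption) and all arms equal, the chance of any false pairwise claim is 1 − (1 − 0.0226)⁶ = 13% with Bonferroni over three and 1 − (1 − 0.043)⁶ = 23% without. Closed testing protects only within one outcome at one visit. The antibody row is in substance one contrast, adalimumab alone against the combination, so the three-arm argument adds little there.

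**Conclusion.** The point holds for the primary outcome. With three arms and nulls of no difference, the requirement of a significant primary test gives strong family-wise control at 5%, and the Bonferroni step is an extra, conservative layer. At 64 per arm it costs each combination comparison about 7 points of power (divisor two) or 13 points (divisor three). The chance of winning both falls by about 11 or 18 points, and of winning at least one by about 4 or 9.

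These figures rest on two-sided testing, rates of 66/43/43% and all 64 per arm in the analysis. Even unadjusted, power to beat both drugs is only about 61%, because the sample size was set on the pooled contrast; removing the penalty does not cure that. The change is worth making because it is nearly free, but keeping Bonferroni would not invalidate the trial.

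**What to change.** For the primary outcome, replace the Bonferroni sentence with:

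> Given a significant primary test, each pairwise comparison (null of no difference) is tested at two-sided 0.05 without further adjustment; closed testing with three arms keeps the family-wise error for this outcome at 5%.

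Before adopting it, confirm that the 5% delta in the sample size section is not a margin for the pairwise tests. If it is, this wording must not be used.

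In Table 4 the same change is optional. Any error-control claim there must be limited to one outcome at one visit and must not be stated as 5% across the signs and visits.

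If the sponsor keeps Bonferroni, for instance for its simultaneous intervals, the plan should state the divisor and the resulting pairwise power.

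**Cost.** One sentence, through the approvals the article requires for relevant modifications, and no added patients. Table 5 lists the trial as not yet recruiting, so on that status the change could be made before any outcome data exist. Actual family-wise error rises from about 1–2% (divisor three) to at most the nominal 5%, and the simultaneous Bonferroni intervals are given up.

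### Table 4 plans about 33 post-baseline secondary tests at an unadjusted 0.05, also lists baseline for testing, and leaves four time-to-relapse versions unranked

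*Protocol article*

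**What the plan says.** All the relevant text is in the protocol article, under the planned methods for efficacy-related objectives, and in Table 4.

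- **Purpose of the secondary analyses.** "Secondary efficacy-related analyses are designed to test the hypothesis that treatment assignment affects a given outcome, after controlling for selected covariates".
- **Mantel-Haenszel rows** (week-16 inactivity, clinical components, anti-adalimumab antibodies). "If p-value<0.05, pairwise comparisons using MHT stratified by NIU location will be carried out with Bonferroni adjustment of the pairwise p-values".
- **EQ5D row.** "P-value<0.05 will be considered as a significant interaction".
- **VFQ-25 and HADS row.** "Changes between Baseline and w16, and the FET visit will be compared between treatment groups using ANOVA". No significance level is written here, and none is written in the visual acuity row, which names only GEE models.
- **Clinical components row.** Five ocular signs plus "loss of CVA secondary to inflammation at baseline, week 16, week 52 and relapse visit".
- **Time-to-relapse row.** "Time to relapse between arms will be analysed using log-rank test at a two-sided significance level of 5" per cent, and then: "We will consider both the time until the onset of the first inflammatory manifestation, each inflammatory manifestation, the first inflammatory manifestation that does not resolve" within four weeks, and each such unresolved manifestation.

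For the primary outcome, one overall contrast is tested first. The pairwise comparisons follow only if it is significant, and they are Bonferroni-adjusted. No rule links the secondary outcomes to one another or to the primary result, and none of them is called exploratory.

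**The concern.** The article does address multiplicity, but for the secondary outcomes it places the adjustment only at the arm pairs within one outcome. Nothing covers the spread over outcomes, visits and endpoint versions, where most of the tests arise. A secondary p-value below 0.05 would therefore carry the label of a hypothesis test, and a reader of the results could not tell how many chances there had been to obtain it.

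Two rows add to this. A comparison of randomised arms at baseline cannot show a treatment effect, so a significant result there is chance by construction. And four relapse versions under one 5% level leave open which of them answers the question, although time to the first manifestation and time to the first unresolved manifestation can disagree.

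**Working it through.** The documents state neither a number of secondary tests nor a family-wise error rate, so there is no figure of the plan's own to reproduce. Both are derived here.

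**Step 1: count the overall tests in Table 4** (before any pairwise follow-up), reading one test per listed visit or version.

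| Row | Count | Level written? |
|---|---|---|
| Complete inactivity by week 16 | 1 | yes |
| EQ5D time-by-arm interaction | 1 | yes |
| VFQ-25 and HADS, 2 scales × 2 changes | 4 | no |
| Clinical components, 6 × 4 visits | 24 | yes |
| Time to relapse, 4 versions | 4 | yes |
| Visual acuity | 1 | no |
| Anti-adalimumab antibodies, 4 times | 4 | yes |

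Total: 1 + 1 + 4 + 24 + 4 + 1 + 4 = 39. A level is written for 1 + 1 + 24 + 4 + 4 = 34 of these and only implied for 4 + 1 = 5. The cost row plans no hypothesis test and is not counted.

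**Step 2: remove baseline.** Six of the 24 component tests are at baseline. That leaves 39 − 6 = 33 tests that could show a treatment effect.

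**Step 3: chance of at least one false positive, all nulls true.** For m independent tests at 0.05 it is 1 − 0.95^m, and the expected number is 0.05 × m.

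- m = 33: 1 − 0.95^33 = 0.816; expected 0.05 × 33 = 1.65.
- m = 39: 1 − 0.95^39 = 0.865; expected 0.05 × 39 = 1.95.

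**Step 4: allow for correlation.** The outcomes overlap: the same signs recur at several visits, and the relapse definitions are nested. The documents give no correlations, so they are assumed. With equicorrelated normal test statistics and rejection at |z| > 1.96:

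| Tests | ρ = 0 | 0.3 | 0.5 | 0.6 | 0.8 |
|---|---|---|---|---|---|
| 33 (after baseline) | 0.82 | 0.69 | 0.53 | 0.44 | 0.26 |
| 39 (all) | 0.86 | 0.74 | 0.57 | 0.47 | 0.28 |

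A block structure for the 33 tests gives 0.64 with correlation 0.7 within and 0.3 between outcomes, and 0.45 with 0.9 within and 0.5 between.

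**Step 5: the two specific rows.**

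- Six baseline component tests: 1 − 0.95^6 = 0.26 if independent, 0.14 at ρ = 0.8.
- Four relapse versions: 1 − 0.95^4 = 0.19 if independent (0.185 before rounding), 0.11 at ρ = 0.8.

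**The case against.** The strongest reply is that an order among secondary outcomes, or an exploratory label, is what an article commonly leaves to the statistical analysis plan. The safety section shows that such a plan is intended. This stands for the missing order taken alone. It does not dispose of the point, because the article goes further than silence: it describes the analyses as hypothesis tests, writes decision thresholds for most rows, and fixes where Bonferroni applies.

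Other replies stand in part.

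- **The count is a reading.** The visits sit in the outcome column of Table 4, and the analysis column does not say one test per visit. The matching objective in Table 1 concerns follow-up, so baseline testing may not be intended. The table nevertheless lists baseline for that analysis, and the wording should be settled.
- **Relapse already has a definition.** Tables 1 and 4 both define it by the appearance of at least one manifestation, so the other versions can be read as supplementary. Table 4 does not say so and gives all of them the same test.
- **Antibodies are a weak basis for an efficacy claim.** Without those four tests, 29 remain, and the rate is 0.77 if they are independent and 0.50 at ρ = 0.5.

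A reader might infer that a false-positive secondary finding is more likely than not. The documents do not support that as a general statement. It needs every null to be true and, for the 33 tests, a common correlation no higher than about 0.5. At 0.6 the figure is already 0.44. A reader might also infer that the plan intends to claim secondary benefit when the primary test fails. The article does not say this. It only fails to rule it out.

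**Conclusion.** The point holds as a matter of interpretation. Table 4 sets out about 33 post-baseline tests at a written or implied 0.05, with adjustment only between arms within an outcome. The chance of at least one false positive among them is roughly 0.26 to 0.82, against 0.05 for a single test. That range rests on all nulls being true, on one test per listed visit or version, and on an assumed common correlation from 0.8 down to 0.

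The baseline listing and the four unranked relapse versions are defects that do not depend on the total count. The primary analysis is sound in this respect: its contrast is named, its pairwise tests are gated, and its error rate is untouched by anything in Table 4.

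**What to change.** 1. In the clinical components row, describe the baseline visit by arm without p-values.
2. Name time to the first inflammatory manifestation, the definition already in Tables 1 and 4, as the time-to-relapse endpoint. Call the other three versions sensitivity analyses.
3. State that the remaining Table 4 analyses are exploratory and will be reported as estimates with 95% confidence intervals, without confirmatory claims of significance.

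The cost is wording in the analysis plan. No patients, visits or primary power are affected. The downside is that an isolated secondary p-value below 0.05 can no longer be presented as confirmatory.

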### Intervention

All subjects entering the study will be centrally randomised at the baseline visit into one of three study arms, in a 1:1:1 ratio:

*Arm 1* will receive at the baseline visit ADA 80 mg SC loading dose followed a week later by 40 mg every-other-week starting at week 1. They will also receive MTX oral at the baseline visit, with initial dose of 15 mg/week, increasing up to 25 mg/week.

*Arm 2*: MTX with the same schedule as in arm 1.

*Arm 3*: ADA with the same schedule as in arm 1.

In addition to the study drugs, topical adjunctive eye medication will be allowed according to standard practice (intraocular pressure-lowering medication, cycloplegic agents, artificial tears, topical non-steroidal anti-inflammatory drugs…). The use of any biologic therapies with a potential therapeutic impact in NIUs, live vaccines, any other ISD besides the study drugs, intraocular GCs implants or intraocular surgery will be prohibited for the duration of the trial.

To ensure a balance of patients across treatment groups and uveitis anatomic locations, patients will be stratified according to the main site of ocular inflammation (intermediate, OR posterior/panuveitis). Randomisation will not be stratified by site due to the small-expected number of subjects per site.

Block randomisation will ensure that an equal number of patients are randomised to each study arm.

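### Table 4 analyses VFQ-25 and HADS changes by unadjusted ANOVA, leaves uveitis location out of the EQ-5D and relapse analyses, and chooses the GEE correlation by a criterion GEE does not supply

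*Protocol article*

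**What the plan says.** All references are to the protocol article.

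- **Stated aim.** The section on planned efficacy analyses says the secondary analyses test for a treatment effect "after controlling for selected covariates" and refers to Table 4 for the details.
- **VFQ-25 and HADS (Table 4).** "Changes between Baseline and w16, and the FET visit will be compared between treatment groups using ANOVA". No baseline score and no stratum term is named.
- **EQ-5D (Table 4).** GEE models "adjusted by study visit (continuous) and treatment arm (discrete) will be carried out", Gaussian with identity link, plus a time-by-arm interaction. On the working correlation: "Different covariable structures will be tested (independent and exchangeable) and compared using the Bayesian Information Criteria".
- **Visual acuity (Table 4).** GEE models, with no terms listed.
- **Time to relapse (Table 4).** "Time to relapse between arms will be analysed using log-rank test at a two-sided significance level of 5" per cent. Only subjects with a good response by week 16 are included, and no strata are named.
- **Randomisation (Intervention section).** "patients will be stratified according to the main site of ocular inflammation", with intermediate uveitis as one stratum and posterior or panuveitis as the other.
- **Use of that stratum elsewhere.** The primary analysis is a Mantel-Haenszel test stratified by location. So are the Table 4 rows for week-16 inactivity, the clinical components and anti-adalimumab antibodies.
- **Baseline data (Table 3).** VFQ-25, HADS, EQ-5D and visual acuity are all scheduled at baseline, or at screening within the 14 days before it.

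**The concern.** Three things in Table 4 do not fit the surrounding text or the method named.

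1. The text promises covariate control, but the ANOVA row has no covariate and the EQ-5D row has none beyond design terms. Since the text refers the reader to Table 4, this is a mismatch within the article and not a detail left for later.
2. Location is a randomisation stratum and is carried into every Mantel-Haenszel row, but not into the ANOVA, EQ-5D or log-rank rows. If location is prognostic, leaving out a factor balanced by design tends to make standard errors too large. The relapse analysis has an added reason to stratify: week-16 responders are selected after randomisation, so balance on location is no longer assured among them.
3. GEE solves estimating equations and has no full likelihood. A BIC is therefore not part of the method, and the row does not say which version is meant.

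At stake is precision in the patient-reported and relapse outcomes, and a correlation structure whose choice would depend on how an analyst reads one phrase.

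**Working it through.** **Base size.** The article gives no power figure for these outcomes; its sample size rests on the primary outcome. For 66% (43% plus 23 points) against 43%, combination arm against both monotherapy arms pooled (1:2), two-sided 0.05 and 80% power, the requirement is 55 (pooled variance) or 54.2 (arcsine) in the combination arm, against the stated 54. Then 54/0.85 = 63.5, which rounds up to the stated 64. I use 64 per arm below.

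**ANCOVA against change-score ANOVA.** Let rho be the correlation of baseline with follow-up. The article does not give it; 0.3 to 0.8 is my assumption. With common variance s²:

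- change score: variance per subject = 2(1 − rho)s²
- ANCOVA: residual variance = (1 − rho²)s²
- ratio = (1 − rho)(1 + rho) / [2(1 − rho)] = (1 + rho)/2

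| rho | Variance ratio | Reduction | 64 per arm acts like (64/ratio) | Pairwise power with ANCOVA where change score has 80% |
|---|---|---|---|---|
| 0.3 | 0.65 | 35% | 98 | 94% |
| 0.5 | 0.75 | 25% | 85 | 90% |
| 0.7 | 0.85 | 15% | 75 | 86% |
| 0.8 | 0.90 | 10% | 71 | 84% |

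For rho of 0.5 to 0.7 the gain equals 1/0.75 = 1.33 to 1/0.85 = 1.18 times the subjects.

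If baseline and follow-up variances differ (s0², s1²), the change-score variance minus the ANCOVA variance is s0² + s1² − 2·rho·s0·s1 − s1²(1 − rho²) = (s0 − rho·s1)². This is never negative, so the direction does not depend on equal variances; only the size does.

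**Simulated three-arm F-test** (64 per arm, 4,000 runs, one arm shifted by 0.4 SD). Power rose from 49% to 69% at rho 0.3, from 65% to 77% at 0.5 and from 86% to 91% at 0.7. With no shift, both methods rejected in about 4.4% to 4.9% of runs, so the planned ANOVA is valid.

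**Location.** The article gives no effect of location on any of these outcomes, so no gain can be calculated.

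**BIC for the working correlation.** Two versions could be meant.

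- *Residual-based:* N·log(RSS/N) + p·log(N). Working independence with Gaussian errors and identity link is least squares, which minimises RSS by construction, and p is the same under both structures. Exchangeable can therefore at best tie. In simulation independence was chosen in every run at within-patient correlations of 0.3, 0.6 and 0.8.
- *Gaussian working likelihood, including the covariance determinant:* this can be computed. With 192 patients, 15 visits, 15% missing at random and 20 runs per setting, it chose independence every time at correlation 0 and exchangeable every time at 0.3 and 0.6.

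The two versions give opposite answers on correlated data, and the phrase "compared using the Bayesian Information Criteria" does not say which applies.

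**The case against.** The strongest reply is that nothing here is invalid. Change-score ANOVA keeps its type I error under randomisation, any error from omitting location is conservative, the primary analysis is stratified, and no power target is set for these outcomes. All of that stands, and it limits the point to precision and clarity in secondary analyses.

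Four stronger readings are tempting, and the document does not support them.

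- *That baseline data are thrown away.* A change score uses baseline by subtraction. What is lost is efficiency and proper adjustment for chance imbalance. For EQ-5D, with visit as continuous time and a time-by-arm term, baseline may well already be the first repeated response.
- *That the visual acuity model omits location.* That row lists no terms at all. Silence in a condensed article shows no omission; the explicit GEE case is EQ-5D.
- *That the working correlation cannot be chosen as written.* A Gaussian working-likelihood BIC can be written down and behaves sensibly. The fair criticism is that BIC is not native to GEE, the version is unnamed, and the simple version has a fixed outcome. With robust standard errors the choice mainly affects efficiency.
- *That baseline can be added to every model without further change.* If baseline EQ-5D is already a response, entering it as a covariate puts the same value on both sides.

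The reply that a later analysis plan may settle these matters is weaker. Table 4 names the methods and terms, and the text presents the table as the detail.

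**Conclusion.** The point holds as a matter of precision and consistency. The promise of covariate control is not met in the VFQ-25, HADS, EQ-5D and relapse rows, and location is used in some rows of one table and dropped in others.

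For VFQ-25 and HADS, ANCOVA would cut variance by about 15% to 25% for a correlation of 0.7 to 0.5, and by 10% to 35% across 0.8 to 0.3. These sizes assume equal baseline and follow-up variances and a correlation the article does not give. ANCOVA would also remove chance baseline imbalance. The benefit of adding location is plausible but cannot be quantified. The BIC rule is non-standard and ambiguous.

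A reader might infer inflated false-positive risk or damage to the primary result. Neither follows: the planned ANOVA holds its level, and the primary test already stratifies by location. The changes are worth making before analysis because they need no new data.

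**What to change.** - **VFQ-25 and HADS:** analyse the week-16 score and the final score by ANCOVA on arm, baseline score and uveitis location.
- **EQ-5D and visual acuity:** add location to the models. State whether the baseline visit is part of the response. If it is, keep it as a repeated response; enter baseline as a covariate only if that visit is removed from the response vector.
- **Time to relapse:** stratify the log-rank test by location.
- **Working correlation:** in place of BIC, pre-specify exchangeable with robust standard errors. Using QIC, or a likelihood-based mixed model, would also do.
- **Text:** name the covariates where the article now says only that selected ones are controlled for.

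The cost is a wording change before analysis and a few extra model terms. If the baseline row is dropped from the EQ-5D or visual acuity model, the time-by-arm term no longer describes change from baseline and its interpretation must be restated.
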